## Background

Headache is a common disorder with a high impact, both on the socio-economic level and on the level of the individual sufferer [1-3]. Not all headache patients seek headache treatment, although severe pain and disability have been reported even in large proportions of non-care seekers [4]. Patients do not look for treatment partially out of ignorance of effective treatments or because of previous negative experiences [2,5].

Guidelines for headache management in primary care are available [6,7]. These guidelines provide diagnostic and therapeutic algorithms and stepped treatment plans for the most common headache types. Apparently they are insufficiently applied in daily practice as patients are frequently referred to neurology clinics after no more than one visit to the general practitioners (GP) office [8].

Physical treatments of the cervical spine, provided by musculoskeletal physiotherapists can be considered as a treatment option in headache sufferers. The effects of musculoskeletal physiotherapy for various headache types are reported both in RCT's and systematic reviews [9-16]. The combination of mobilisations and low-load exercises focussing on the cranio-cervical flexion is of particular interest nowadays [9,13]. The conclusions of systematic reviews are not firm due to methodological limitations of the selected studies, but there are indications that musculoskeletal physiotherapy directed to the cervical spine can be beneficial for some headache patients [11,15]. Reductions in headache frequency, intensity and duration of headache attacks have been reported [9,13]. Dowson et al. recommend physical therapy (muscle relaxing and mobilising exercises) for those patients who report neck stiffness [17,18]. The neck-headache relationship is however not always causal: neck pain experienced by migraine patients for example can be a result of sensitization [19]. The co-existence of headache and neck pain and/or the presence of neck stiffness might therefore not be a sufficient indication to prescribe physical treatment of the cervical spine.

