These therapeutic uncertainties contribute to patients' treatment dissatisfaction. Relatively high percentages of headache sufferers are not satisfied with the headache care they receive. Harpole and co-workers investigated the headache burden and patient satisfaction with existing management in primary care, using patient-administered surveys. Of the 385 responders, who all contacted a GP because of their headache, 48 % reported problems with headache management and 17 % were dissatisfied with the headache care. Patients with a high headache-related impairment reported more problems with their headache management [20]. Walling et al. found that 26 % were dissatisfied in their sample of 447 migraine patients [21].

The prevalence and burden of headache, the dissatisfaction percentages and the diversity in headache treatments, call for a refinement of headache management.

The identification prior to the start of a treatment, of patients whom might react properly to the treatment, is necessary to reduce the risk of a negative outcome. For this purpose, patient characteristics which predict the treatment outcome (prognostic characteristics) need to be determined.

Prognostic factors are multifactorial. Jull and Stanton analysed the results of 152 CErvicogenic Headache (CEH) patients who participated in one of the three active treatment groups in a headache trial [9]. The prognostic value of socio-demographic factors, headache features, physical impairments of the cervical spine, neck pain and disability and patients' perceptions of influences on their headaches (locus of control) was investigated. They were unable to identify a systematic pattern of prognostic factors. Only the presence of light-headedness appeared to be a clinically relevant predictor of a bad outcome. Of the physical tests only joint pain on palpation had a prognostic value [22]. Of their tests only this palpation could be used for prognostic uses.

Our study has a double aim. Our primary aim is to analyse the prognostic value of a series of physical tests. Our secondary aim is to compare two currently applied treatment strategies, being the usual care (UC) administered by a medical doctor following a stepped guideline [7], and the UC plus a musculoskeletal physiotherapy treatment protocol (UCMT), described by Jull et al [9].

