### In- and exclusion criteria

Dutch speaking patients with a combination of recurrent headache and neck pain since minimum two months and at least twice a month with an active help-request (who consider to undergo treatment) are recruited. They have to be at least 18 years old and be willing to participate. Subjects are excluded in case of cluster headache or trigeminal neuralgia. To avoid false positive tests with the quantitative sensory tests (see description of measurements), patients with peripheral neuropathies and co-morbidity of chronic musculoskeletal pain will be excluded. Because of the neck mobility tests, people with rheumatoid arthritis, Down syndrome and/or a history of neck surgery will be excluded. The presence of red flags for headache (warning signs for serious causes of the headache) is an extra exclusion criterion. Pregnant women are also excluded, as pregnancy influences the frequency and intensity of headaches with migraine properties.

To avoid biased patients (with treatment preferences), we excluded patients who received physiotherapy treatment for their headaches during the last 12 months or patients whose prescribed medication was changed during the last two months.

The included headache types are migraine, tension-type headache and CEH. For migraine and tension-type headache the IHS criteria are used [26], for CEH the criteria of the Cervicogenic Headache International Study Group (CHISG) [27].

For the patients recruited via internet sites and advertisements, an additional exclusion criteria is set: a HIT-6 score of at least 56 points. From this level, the HIT-6 scoring advises the patient to contact his/her GP in order to start a treatment [28].

All subjects sign a written informed consent.

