### Interventions

The UCMT group will receive a musculoskeletal physiotherapy treatment during 6 weeks following the protocol described by Jull et al. [10,11]. It consists of a combination of spinal mobilisations and exercise therapy. Spinal mobilisations consist of low and/or high-velocity cervical joint mobilization techniques. Each therapist can decide the technique of choice based on his own clinical skills and the patient's situation. Therapeutic exercises consist of low-load endurance exercises, more precisely cranio cervical flexion exercises. A maximum of 12 sessions (twice a week over a period of 6 weeks) is provided. Each session lasts approximately 30 minutes.

All participants receive a letter containing recommendations for treatment, based on the available evidence. This letter is to be handed over to the therapist. After the six weeks treatment period, the therapists will be contacted by phone to check for treatment integrity.

As a guideline for the UC treatment, the protocol from the Dutch College of GPs is used. It consists of a stepped approach to diagnose and treat primary headache disorders. In the Flemish part of Belgium this is the guideline with the lowest access threshold. The GP receives an email containing a weblink to the Dutch College of GPs guideline [7]. In this treatment group treatment integrity will be analysed via the Headache Inventory List, which is to be completed in the follow-up measurements.

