### Randomisation

After baseline measurements patients are randomised. Subjects are randomised using blinded envelopes, using a pre-stratification for the headache diagnosis. So, an envelope for migraine, tension-type headache and CEH is provided. Each envelope contains 10 notes, five mentioning usual care and five mentioning usual care plus manual therapy. This to ensure that for each 10 patients with the same diagnosis, the same number of patients is randomised in one of the two treatment groups. Due to the randomisation after testing all tests are performed by a blinded rater.

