### Statistical analyses, power and sample size calculation

The prognostic capacity of the initial series of tests (physical examination of the cervical spine and QST) will be calculated by means of a logistic regression analysis, comparing the results of the responders with those of the non-responders. Instead of starting with a full regression model, two known prognostic factors, derived from the study from Jull and Stanton [8] will be included in the analysis a priori. Those two factors are 'light-headedness' and 'joint pain on palpation'. Consequently a backwards stepwise selection will be used, including the two known factors in the smaller models. Differences at baseline between the two treatment groups will be included in the regression models as potential prognostic factors. The plausibility of the signs will be considered to check the logical contribution of each factor in the model. The power of the obtained models will be analysed via the area under the ROC-curve.

Group differences and effect sizes can be calculated for headache intensity and frequency, medication intake, HIT-6 scores and absenteeism. The number of responders and non-responders in both groups will be compared. GPE is a dichotomous variable. Sample size calculations with a significance level of p < 0.05, an event rate of 0.50 in the usual care group and of 0.70 in the usual care plus musculoskeletal physiotherapy group a power of 80% and an equal amount of subjects in both treatment groups result in a sample size of 93 subjects in each treatment group. This results in a total of 186 subjects.

The results of all subjects will be analysed, regardless of their treatment adherence (intention-to-treat analysis).

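### The pooled usual-care versus physiotherapy comparison makes no use of the randomised diagnosis strata, although background care and the added effect may differ in cervicogenic headache

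*Protocol article*

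**What the plan says.** The secondary aim (Background) compares "the usual care (UC) administered by a medical doctor following a stepped guideline" with that same care plus a physiotherapy protocol directed at the cervical spine. Under Interventions, the guideline that defines UC is described in one sentence on scope: "It consists of a stepped approach to diagnose and treat primary headache disorders". The Background describes the available headache guidelines more loosely: "These guidelines provide diagnostic and therapeutic algorithms and stepped treatment plans for the most common headache types".

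The In- and exclusion criteria state: "The included headache types are migraine, tension-type headache and CEH". Migraine and tension-type headache are diagnosed by IHS criteria, and CEH by a separate set from its own study group. Randomisation is stratified by diagnosis: "So, an envelope for migraine, tension-type headache and CEH is provided". Within each envelope the split is even: "Each envelope contains 10 notes, five mentioning usual care and five mentioning usual care plus manual therapy".

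For the treatment comparison, the section on statistical analyses, power and sample size says: "The number of responders and non-responders in both groups will be compared". It also says that group differences can be calculated for HIT-6 and other measures. One pair of responder rates, 0.50 and 0.70, is assumed for all patients, giving 93 per arm. The article describes neither an adjustment for diagnosis nor a comparison by diagnosis.

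**The concern.** CEH has its own criteria and its own envelope, but the only description of usual care is a guideline whose stated scope is primary headache. The article does not say what the guideline offers CEH patients. The added treatment acts on the neck. Both the background care and the gain from adding physiotherapy could therefore differ between CEH and the other two diagnoses.

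The article itself gives reason to expect this. The Abstract says physiotherapy can succeed only where there is an underlying cervical segmental dysfunction. The Background says that the link between neck and headache is not always causal, and that neck pain in migraine can reflect sensitisation.

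What is at stake is the use of the result. The Abstract aims at more correct referrals to physiotherapy. One pooled difference does not tell a referring doctor whether the gain lies in migraine, in tension-type headache, in CEH or in all three. The Discussion plans to check whether centres can be pooled; the article states no similar check for diagnosis, the factor on which patients are randomised.

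**Working it through.** **Inputs from the article.** Responder rates 0.50 (UC) and 0.70 (UCMT), significance level 0.05, power 80%, equal arms, 93 per arm, and three diagnosis strata allocated 5:5 in tens. Two-sidedness is not stated, but it reproduces the figure.

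**Assumed inputs.** The article gives neither the share of CEH nor any diagnosis-specific rate. I take a CEH share of one third, and show 10% to 50% where it matters.

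**1. The plan's own figure.** Two proportions, pooled variance under the null, no continuity correction, mean rate 0.60:

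n = [1.96 × √(2 × 0.60 × 0.40) + 0.842 × √(0.50 × 0.50 + 0.70 × 0.30)]² / 0.20²

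= [1.358 + 0.571]² / 0.04 = 93 per arm. Power at 93 per arm is 80.0%. The stated size reproduces.

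**2. Different patterns can give the same pooled difference.** With CEH share f, each arm's pooled rate is (1 − f) × (rate outside CEH) + f × (rate in CEH). Take f = 1/3 and 93 per arm:

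| Assumed pattern | Outside CEH, UC / UCMT | CEH, UC / UCMT | Pooled UC / UCMT | Difference | Power |
|---|---|---|---|---|---|
| Gain only in CEH | 0.50 / 0.50 | 0.30 / 0.70 | 0.433 / 0.567 | 0.133 | 44% |
| Gain only outside CEH | 0.50 / 0.70 | 0.50 / 0.50 | 0.500 / 0.633 | 0.133 | 45% |

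The pooled difference is 13.3 points in both rows, yet they imply opposite referral advice. The pooled analysis cannot tell them apart. Both rows are illustrations, not expectations.

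**3. How much a stratum can show.** Power within CEH for 0.50 versus 0.70, same formula:

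| CEH share | CEH per arm | Power |
|---|---|---|
| 10% | 9 | 13% |
| 20% | 19 | 24% |
| one third | 31 | 36% |
| 50% | 47 | 51% |

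At one third, the standard error of the CEH difference is √(0.46 / 31) = 0.122, where 0.46 = 0.25 + 0.21. The 95% half-width is 1.96 × 0.122 = 0.24. For the other two diagnoses together, with 62 per arm, it is 1.96 × √(0.46 / 62) = 0.17, and power for 0.50 versus 0.70 is about 63%.

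**4. Arm-by-diagnosis term (CEH versus the rest).** Its standard error is √(0.46 / 31 + 0.46 / 62) = 0.149. Power to detect a 0.20 difference between the two effects is Φ(0.20 / 0.149 − 1.96) = Φ(−0.62), or about 27%. The term describes heterogeneity; it cannot exclude it.

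**The case against.** A reader might infer that CEH control patients do not receive guideline care, so that the pooled difference mixes two contrasts. The article does not support this:

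- Nowhere does it say that the guideline omits CEH or that CEH is not a primary headache. The separate criteria concern diagnosis, and the Background speaks only of the most common headache types. The guideline's content is not available here.
- In every diagnosis the randomised contrast is the same: UC against UC plus physiotherapy, allocated 1:1. Diagnosis cannot confound the pooled difference, which is an unbiased average over the patients enrolled.

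A reader might also take the first row of the illustration as a risk of a false-positive result. It is not. In that row the pooled effect is real, and the same numbers would arise if the guideline covered CEH fully and physiotherapy simply worked better there. They show heterogeneity of effect, not a faulty comparator.

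It can also be said that enrolling all three diagnoses is an open choice, argued in the Discussion; that the treatment comparison is the secondary aim, with prognostic factors primary; and that stratified models are often left to an analysis plan, which is not shown. All of this stands, and it makes the point a modest one. What remains is that the article stratifies on diagnosis, expects the effect to depend on cervical involvement and wants to guide referral, yet describes its treatment comparison as a single pooled count.

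**Conclusion.** The point holds as one of interpretation and analysis, not of bias or sample size. The stated scope of the UC guideline is primary headache, and no usual care is described for CEH, so background care and the added effect may differ by diagnosis. The pooled comparison is valid, and 93 per arm is correct for the stated rates. As described, it leaves the randomisation strata unused and cannot locate the benefit.

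The size of any difference between diagnoses cannot be derived from the article. What can be said is that diagnosis-specific results will be imprecise: about 36% power in CEH at an assumed one-third share (13% to 51% for shares of 10% to 50%), and about 27% for a 20-point difference in effect. They should be presented as estimates. The material supports neither restricting the main conclusion to migraine and tension-type headache nor describing CEH control care as outside the guideline.

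**What to change.** In the statistical analysis section:

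- Keep the pooled responder comparison as the powered test, and adjust it for the randomised diagnosis: a logistic model for responder status with arm and diagnosis. Treat HIT-6 likewise, with arm and diagnosis in its model.
- Report the UCMT minus UC difference with 95% CI for each diagnosis, together with an arm-by-diagnosis term. Label these as estimates and state that power within a stratum is low.
- When interpreting the result, note that the cited guideline is described as covering primary headache only. Do not go further by calling CEH control care non-guideline or by drawing the main conclusion from two strata.

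The cost is a few sentences and one further model. Diagnosis is already recorded and randomised on, so no new data or patients are needed. The price to accept is wide intervals by diagnosis: roughly ±24 points in CEH at a one-third share. Restricting the main claim to the other two diagnoses would cost more, since power would fall from 80% to about 63%; that is a further reason to keep the pooled test.

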### Randomisation

After baseline measurements patients are randomised. Subjects are randomised using blinded envelopes, using a pre-stratification for the headache diagnosis. So, an envelope for migraine, tension-type headache and CEH is provided. Each envelope contains 10 notes, five mentioning usual care and five mentioning usual care plus manual therapy. This to ensure that for each 10 patients with the same diagnosis, the same number of patients is randomised in one of the two treatment groups. Due to the randomisation after testing all tests are performed by a blinded rater.

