## Methods/design

### Study design

A randomised clinical trial with blinded assessment and unblinded treatment and with a follow-up period of 12 months was developed. The research protocol was approved by the Medical Ethics Committees of the University Hospital of the Vrije Universiteit Brussel (UZ Brussel) and of the University Hospital of Antwerp (UZA).

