### Baseline measurements

Baseline measurements consist of two parts: the completion of questionnaires and physical tests. All baseline measurements are performed by a blinded examiner/rater, as subjects are allocated at random after the baseline measurements (see below: Randomization).

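### A fixed, published draw of five notes per arm for each diagnosis lets late assignments be inferred, so testing before randomisation does not by itself secure rater blinding or concealment

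*Protocol article*

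**What the plan says.** The Randomisation section of the protocol article fixes the allocation method.

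- **Strata:** "Subjects are randomised using blinded envelopes, using a pre-stratification for the headache diagnosis". There is one container per diagnosis: "So, an envelope for migraine, tension-type headache and CEH is provided".
- **Content:** "Each envelope contains 10 notes, five mentioning usual care and five mentioning usual care plus manual therapy".
- **Purpose:** exact balance after every tenth patient in a diagnosis. The article's sentence on this begins "This to ensure that for each 10 patients with the same diagnosis, the same number of patients is randomised in one of the two treatment".

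The Study design section describes "A randomised clinical trial with blinded assessment and unblinded treatment".

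Blinding of the baseline tests is argued from their order alone, in two places. The Baseline measurements section says "All baseline measurements are performed by a blinded examiner/rater, as subjects are allocated at random after the baseline measurements". The Randomisation section repeats the inference: "Due to the randomisation after testing all tests are performed by a blinded rater".

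**The concern.** Ten notes of known composition, drawn without replacement, form a permuted block of fixed and published size. Once five notes of one kind are out, the rest of that block is known to anyone who has kept count. Somebody on the study side must learn allocations, because the Interventions section has the physiotherapists telephoned after the six-week treatment period.

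Testing before the draw keeps the rater blind only if the coming allocation cannot be foreseen. If it can, two things are at stake:

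- **Selection at enrolment.** A patient could be entered now or deferred according to the arm that is due. The Discussion acknowledges that clinicians have treatment preferences and that these can affect which patients are referred.
- **Baseline scoring.** The physical tests are the candidate predictors for the primary aim. The rotation test is scored partly on mobility and endfeel, which are examiner judgements. If foreknowledge of the arm coloured those scores, and the arm affects response, part of an apparent prognostic association could come from the arm.

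**Working it through.** **Inputs.** Block of 10, five per arm, and three strata (Randomisation). Total of 186 patients (Statistical analyses, power and sample size calculation). The article gives no predictability figure.

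**The plan's own figure.** The 186 serves here only as a denominator. For 0.50 versus 0.70, two-sided alpha 0.05 and power 80%, with pooled variance under the null and no continuity correction:

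n = [1.96·√(2·0.6·0.4) + 0.8416·√(0.25 + 0.21)]² / 0.20² = (1.358 + 0.571)² / 0.04 ≈ 93 per arm, 186 in total.

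The stated size is reproduced and is not in dispute.

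**Assignments certain before the draw.** Suppose an observer knows all earlier draws in the current block. There are C(10,5) = 252 equally likely orders. Draw k+1 is certain if one arm is used up within the first k draws, which has probability 2·C(k,5)/252:

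| Draw | Calculation | Certain beforehand |
|---|---|---|
| 1st to 5th | – | never |
| 6th | 2·1/252 | 0.8% |
| 7th | 2·6/252 | 4.8% |
| 8th | 2·21/252 | 16.7% |
| 9th | 2·56/252 | 44.4% |
| 10th | 2·126/252 | 100% |

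The sum is 2·(1 + 6 + 21 + 56 + 126)/252 = 420/252 = 1.67 per block, or 16.7%. The closed form 2m/(m+1) with m = 5 agrees. Applied to all patients, 0.1667 × 186 = 31.

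Since 186 is not a multiple of 10, 31 is slightly too high. If each diagnosis had 62 patients (an assumption; the article gives no split), there would be six full blocks per stratum, so 3 × 6 × 1.667 = 30 certain assignments, or 16.1%.

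**Best guess.** The observer always names the arm with more notes left and tosses a coin when they are equal. With m = 5:

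m + (4^m/C(2m,m) − 1)/2 = 5 + (1024/252 − 1)/2 = 6.53 correct out of 10, or 65.3%.

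Over 186 patients this is about 121 correct, against 93 (50%) under simple randomisation. Enumerating all 252 orders gives the same 1.67 and 6.53. It also shows that one arm has a probability of at least 75% before 23.9% of draws.

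**What varying the block size achieves.** Simulation with 62 patients per stratum, for an observer who knows the possible sizes and all earlier draws but not where blocks begin and end. The alternative sizes are assumptions for illustration:

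| Block sizes | Certain | Best guess right |
|---|---|---|
| 10 (as planned) | 16.1% | 64.9% |
| 8, 10, 12 | 1.4% | 64.8% |
| 6, 8, 10 | 1.6% | 66.1% |
| 4, 6, 8 | 2.4% | 67.8% |

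Varying the size removes nearly all certain assignments but does not reduce best-guess accuracy. Only withholding the allocation history does that.

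**The case against.** The strongest reply is that every figure above needs an observer with a complete tally per diagnosis, and the article names no such person among recruiters or raters. Open treatment means that patients and treating clinicians know the arm; it does not mean that the baseline examiner does. Who draws the note and how it is logged are details that a condensed article may leave to the full protocol, so their absence is not a fault. This stands, and it makes the risk conditional.

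Other parts of the reply also stand:

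- Recruitment runs through GP practices, two academic neurology clinics and advertisements, while the envelopes are described per diagnosis and not per centre. A GP who sees only their own patients could hardly count a block. Someone with central oversight could.
- Steering a patient into a particular stratum is constrained by published diagnostic criteria and a standardised questionnaire.
- The two primary outcomes, global perceived effect and HIT-6, are reported by patients, and paper forms are entered by a blinded rater. The baseline examiner cannot alter them directly.
- Thermal and pressure thresholds rest on the patient's response, and the pain provocation test is called positive on the patient's own VAS rating. The exposure is mainly in mobility and endfeel.

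The article does call the envelopes blinded. That may hide the next note from view, but the inference comes from the known content and not from seeing a note.

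A reader might go further and infer that notes could be looked at and put back, that the rater was in fact unblinded, or that all assignments were predictable. The documents do not support this. They describe no such handling, do not say that the rater learns earlier draws, and fix a scheme in which half of each block is never certain in advance.

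**Conclusion.** The point holds in a limited form. The weakness lies in the mechanism as stated and is not a matter of missing detail: a fixed, published block of ten per diagnosis, with open treatment, allows late draws to be inferred by anyone who knows the earlier ones. The ceiling is about one assignment in six known with certainty and 65% guessable. It assumes full knowledge of the stratum's history, complete blocks, and a fresh set of ten after each tenth patient. These figures measure predictability; they do not estimate bias in any result.

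It follows that order of testing is not sufficient ground for the statement "Due to the randomisation after testing all tests are performed by a blinded rater", nor does it by itself prevent selection at enrolment. Whether either problem arises depends on the recruiter or rater knowing earlier allocations, which the article neither states nor rules out. It would be wrong to conclude that blinding has failed. The change is worth making because it is cheap.

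**What to change.** Replace the drawing of notes with a computer-generated 1:1 list, stratified by the three diagnoses, in randomly varying block sizes that are not disclosed to recruiters or the rater. The list should be prepared and held by a person with no part in recruitment or baseline testing. Each allocation should be released singly, after that patient's baseline data have been recorded, through sequentially numbered, sealed, opaque envelopes (one per patient) or by central release.

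Keep recruiters and the baseline rater unaware of earlier allocations. This part is essential, because varying the blocks alone leaves best-guess accuracy near 65%. Reword the two sentences on baseline blinding so that they rest on this separation as well as on the order of events.

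The cost is a one-off list and pre-packed envelopes or a central release service. The ratio, the three strata and the total of 186 are unchanged. The arms may differ by a few patients within a stratum: an unfinished block can leave a difference of at most half its size, so up to 6 with a largest block of 12, against up to 5 under the present scheme.
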